#### Intervention

We will implement the multilevel intervention developed in Aim 2. We anticipate that this intervention might contain a training or series of trainings in conjunction with other systems changes, such as changing workflows and communication pathways. For this study, the intervention will be delivered by study team members but we anticipate that in the future it can be developed by local clinical team members. We will develop a full intervention manual following Aim 2 with input from the Expert Panel.

#### Training

To ensure the intervention is implemented consistently and all procedures are followed and assessed, the research team will facilitate and deliver the intervention components. A training on the intervention will be developed and refined to ensure consistent intervention delivery in the future and across hospitals. This will be consistent with our prior work [82, 83], and include information on hospital-level tailoring of the intervention. Training will also ensure consistency and accurate assessment of study outcomes.

#### Measures

We selected outcomes and covariates for this study in alignment with our prior work, expert guidance, and the conceptual framework. As a pilot study, the primary measures, in addition to assessing feasibility and recruitment in the trial, will focus on early implementation outcomes, including provider perception of the intervention's feasibility, acceptability, and appropriateness at their hospital. These will be assessed via brief, previously validated measures [61]. These items (4 questions for each measure) will be completed at 1 and 6 months following the completion of the intervention. To assess for feasibility of the study design and procedures, we will also track hospital and clinician recruitment and retention across the study.

The study will also assess preliminary effectiveness of the intervention. *Communication quality*, as measured by the CritCom survey, is the primary effectiveness outcome. This outcome will be calculated as changes in CritCom score (communication quality) from baseline to 6 months. The CritCom measure is collected at the individual level but will be analyzed as a hospital-level outcome, reflecting overall changes in hospital communication quality. Clinicians will be asked to complete the CritCom assessment and accompanying demographic questions at enrollment, one month after intervention delivery, and at the conclusion of the pilot (6 months after intervention). These time points are selected to allow for preliminary identification of when communication quality changes begin and align to the implementation outcome measures as described above.

In addition to impact on communication quality, we will explore intervention impact on secondary provider and patient effectiveness outcomes. *Provider outcomes* include burnout and retention and *patient outcomes*include clinical deterioration event mortality and safety/adverse events (cardiopulmonary arrest, cardiac arrest) [84]. These are considered exploratory as the trial is not powered to evaluate intervention effectiveness. We will evaluate these exploratory outcomes at three time points: baseline, three months after intervention, and six months after intervention. Provider outcomes will be based on self-report survey items collected along with the CritCom survey and demographic information. Patient outcomes will be reported by site leads via a de-identified prospective registry of all clinical deterioration events, defined as unplanned transfers to intensive care (ICU), the use of ICU interventions on general wards, or unplanned death on the ward [12]. All exploratory outcomes will be assessed as changes from baseline at 6 months.

#### Individual and hospital-level covariates

Participant-level demographic covariates include profession, role on the team, years working at the hospital, and sex. Hospital-level covariates include hospital type, funding structure, country income-level, staffing ratios, bed capacity, and annual new cancer diagnoses managed at the hospital per year.

#### Data collection

Implementation outcomes, communication quality (CritCom), demographic questions, and provider outcomes will be collected at the individual provider level. As described, eligible participants are clinicians who provide care to hospitalized children with cancer at risk of deterioration. Surveys will be distributed to study participants via confidential REDCap links at baseline, one month after the intervention, and at the study's completion (six months post-intervention). Hospital-level information and patient outcomes (clinical deterioration events) will be collected at the hospital level by the site lead. A de-identified report form will be completed by the site lead, or their delegate, for each deterioration event and will be entered into a REDCap database at the three data collection time points, consistent with our prior work [85–87]. Research team coordinators will complete analysis checks for missing and incomplete data and iteratively provide feedback to study teams.

#### Data analysis

Data will be managed, cleaned, and analyzed in R. As a pilot, this study is not powered to formally test effectiveness, and data analysis will focus on the feasibility of the intervention and procedures in preparation for a future trial. Data will be reported using descriptive comparisons by randomization assignment. We will describe participant and hospital characteristics overall and separately by arm. Categorical variables will be reported as N (%) and continuous variables will be reported as mean ± SD or median and interquartile range, as appropriate.

The measures of feasibility, appropriateness, and acceptability are assessed on a 5-point Likert scale. Therefore, we will report descriptive statistics of these measures prior to assessing variation via Kruskal–Wallis and Mann–Whitney tests. Data will be analyzed both at the individual and organization levels, to understand how individual and organizational factors influence intervention feasibility, appropriateness, acceptability and preliminary effectiveness. Recruitment and retention across the study will also be reported via descriptive statistics to assess feasibility of the study design and procedures for a future trial.

To evaluate the preliminary effectiveness of the intervention on perceived communication quality, we will use a linear mixed model approach where intervention is included as a fixed effect (intervention or control) along with randomization assignment, baseline score, time, and the interaction between time and intervention. We will evaluate the preliminary efficacy using a linear contrast to estimate the mean difference in communication quality (CritCom scores overall and by domain) from baseline to 6 months. To account for clustering due to individual- and hospital-level repeated measurements, we will include random terms for both in our mixed model. Exploratory provider and patient outcomes will be compared between the two randomization arms using the same mixed-effect analytic approach described for the primary effectiveness outcome. We will also conduct hospital-specific subgroup analyses to explore heterogeneity in intervention effects across hospitals.

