### Study measures

Study measures (Table 2) align with our conceptual model, including measures of care inputs, team communication, care processes, and multilevel outcomes.

**Table 2 Tab2:** Overview of study measures

Data Domain	Measures	Data Collection Methods
Communication quality	CritCom (6 domains, 30 questions)^a^	- Individual survey, distributed confidentially and electronically through REDCap [60] - Distributed to all frontline clinical staff caring for children with cancer at risk of deterioration at each participating hospital - 3 weeks for data collection with weekly reminders
Individual demographics	6 questions on role, unit worked, length of experience, sex, and hospital of employment	
Provider outcomes	Questions about burnout, intent to leave, and job satisfaction	
Hospital characteristics	Hospital type, funding, bed capacity, pediatric oncology/critical care staffing, annual new diagnoses, and region	- Collected and confirmed by local site lead
Communication structures	Social network survey using a roster-based approach asking clinicians about overall communication patterns and changes during deterioration events^a^	- Individual survey distributed confidentially through REDCap, 20–30 min. to complete - Distributed to all frontline clinical staff caring for children with cancer - 3 weeks for data collection with weekly reminders
Challenges to communication and potential communication interventions	Perspectives of clinicians on communication challenges related to hospital and individual barriers, as well as potential interventions to improve team communication during care delivery	- Semi structured interviews of frontline clinicians caring for children with cancer (physician, nurse, respiratory therapy, etc.) - Purposive sample for diversity including country income level, hospital size, professional role, etc
Intervention feasibility, acceptability, and appropriateness	After intervention implementation, measures to assess how individual clinicians view the feasibility of intervention and their ratings of how appropriate and acceptable it is for them to receive the intervention in their setting	- Individual survey, distributed confidentially through REDCap, 5 min. to complete - Distributed to all frontline clinical staff caring for children with cancer at 8 hospitals - 3 weeks per hospital for data collection, with weekly reminders

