#### Implementation outcomes

During Aim 3, we will conduct surveys of the clinical team members receiving the intervention to assess perceived feasibility, acceptability, and appropriateness of this intervention in their unit/team. We will use brief, validated measures of these constructs [61].

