#### Randomization to intervention

We will use a parallel-arm, pilot cluster-randomized wait list-controlled trial to evaluate the intervention compared to control. A wait list control is a group that does not receive an intervention during the study period, serving as an untreated comparison during the study, although they will receive the intervention after study completion [81]. This methodology was selected due to ethical concerns of restricting interventions in these settings. We will balance randomization on baseline CritCom scores to ensure distribution of communication quality across groups. Hospitals will be randomized to either the multilevel intervention or a wait list control using a 1:1 ratio via randomization protocol generated by the study biostatistician and implemented through REDCap’s randomization module. All baseline hospital and participant data will be collected prior to randomization.

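### Aim 3's primary clinician ratings get rank tests with no allowance for hospital clustering or repeat ratings, and the article conflicts on whether 8 hospitals or only recipients supply them

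*Protocol article*

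**What the plan says.** **Status of the outcomes.** Under Measures (Aim 3), "the primary measures, in addition to assessing feasibility and recruitment in the trial, will focus on early implementation outcomes", meaning clinicians' ratings of feasibility, acceptability and appropriateness. Each clinician rates twice, 1 and 6 months after the intervention is completed.

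**Planned analysis.** Under Data analysis (Aim 3), "we will report descriptive statistics of these measures prior to assessing variation via Kruskal–Wallis and Mann–Whitney tests". The next sentence gives the purpose: "Data will be analyzed both at the individual and organization levels, to understand how individual and organizational factors influence intervention feasibility, appropriateness, acceptability". The comparison groups are not named. The organizational factors available are those in the section on individual and hospital-level covariates: hospital type, funding, country income level, staffing, beds and yearly diagnoses. Each takes one value per hospital.

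**Clustering elsewhere.** For CritCom the same section states: "To account for clustering due to individual- and hospital-level repeated measurements, we will include random terms for both in our mixed model". That approach is extended to the exploratory provider and patient outcomes, but not to the implementation ratings.

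**Who rates.** Table 2 has the survey "Distributed to all frontline clinical staff caring for children with cancer at 8 hospitals", after implementation. The Implementation outcomes section says "we will conduct surveys of the clinical team members receiving the intervention". Under Randomization to intervention, wait-list hospitals get nothing during the study period, "although they will receive the intervention after study completion". Data collection (Aim 3) places the last survey at the end of the study.

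**The concern.** There are two separate problems, and both bear on the pilot's primary measures.

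1. **Independence.** Kruskal–Wallis and Mann–Whitney tests treat every observation as independent. Clinicians in one hospital rate the same delivery in the same setting, so their ratings are likely to be correlated. A factor such as funding structure varies only between hospitals, so the real replicate is the hospital: 8 at most, or 4 if only recipients rate. A clinician-level rank test of such a factor counts respondents instead, and its p-values are too small. Pooling the 1- and 6-month ratings would add a second dependence, within clinician.

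2. **Denominator.** The article gives two answers to which hospitals supply the ratings. If all 8 were surveyed during the trial, half would be rating something that they had not received.

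At stake are any statements about which organizational factors go with better ratings, and the number of hospitals behind the primary descriptive results. Both feed the design of the larger trial that this pilot is meant to prepare.

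**Working it through.** The article gives no ICC, no number of respondents per hospital and no significance level for these tests, so there is no stated figure to reproduce.

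**Inputs**
- Hospitals: 8 (Study settings and recruitment). Allocation: 1:1 (Randomization to intervention). Hospitals per arm: 8/2 = 4; this is derived, not written.
- Respondents per hospital, m: assumed 20, 40 or 60.
- ICC: assumed 0.01, 0.05 or 0.10.
- Nominal two-sided level: assumed 0.05.

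**Step 1. Clinician-level test of a hospital-level factor.** The design effect is DE = 1 + (m − 1) × ICC. The approximate true error rate of an unadjusted test is 2 × [1 − Φ(1.96/√DE)]. Example with m = 40 and ICC = 0.05: DE = 1 + 39 × 0.05 = 2.95; 1.96/√2.95 = 1.14; error about 25%. The approximation was checked by simulating Mann–Whitney tests with no true difference, on 1-to-5 scores with a hospital random effect (3,000 runs per cell):

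| ICC | m | DE | Formula | Simulated, 4 v 4 hospitals | Simulated, 2 v 2 hospitals |
|---|---|---|---|---|---|
| 0.01 | 20 | 1.19 | 7.2% | 6.7% | 6.2% |
| 0.01 | 40 | 1.39 | 9.6% | 8.3% | 10.1% |
| 0.01 | 60 | 1.59 | 12.0% | 10.8% | 11.8% |
| 0.05 | 20 | 1.95 | 16.0% | 15.8% | 16.1% |
| 0.05 | 40 | 2.95 | 25.4% | 23.2% | 25.0% |
| 0.05 | 60 | 3.95 | 32.4% | 29.1% | 32.0% |
| 0.10 | 20 | 2.90 | 25.0% | 22.2% | 24.0% |
| 0.10 | 40 | 4.90 | 37.6% | 36.5% | 36.4% |
| 0.10 | 60 | 6.90 | 45.6% | 44.4% | 45.7% |

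With ICC = 0 the simulated rate is 4.5–5.1%, so the excess comes from clustering.

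**Step 2. Uses that are not affected.** For a factor split evenly within each hospital (profession, for instance), the simulated rate stays at about 4–6% throughout (1,500 runs per cell). Kruskal–Wallis with hospital itself as the factor asks whether these particular hospitals differ, and the shared hospital effect is then what is being tested. Both statements assume one rating per clinician.

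**Step 3. Organization-level test.** With one summary per hospital, the smallest exact two-sided rank-sum p is 2/C(n, n/2):
- 4 v 4 hospitals: 2/70 = 0.029
- 2 v 2, within the 4 intervention hospitals: 2/6 = 0.33, which can never reach 0.05

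**Step 4. Who can rate.** Eight hospitals at 1:1 leaves 4 that receive the intervention during the trial. The other 4 receive it after the study ends, and the last survey is at the end of the study. So at every scheduled survey only 4 hospitals contain recipients, against the 8 in Table 2. If hospital-level summaries have equal variance, 4 instead of 8 widens the standard error of an overall mean by √(8/4) = 1.41.

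**The case against.** **The harmful test is not spelled out.** The comparison groups are unnamed, and "Data will be analyzed both at the individual and organization levels" can be read as pairing individual factors with clinician-level data and organizational factors with hospital-level data. On that reading the inflated test is never run. This stands as a limit: the inflation is conditional. It does not remove the point, because the wording equally permits organizational factors to be tested on clinician-level data, and no adjustment is given for that case.

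**A reader might infer a planned significance test between arms on these ratings, setting recipients against clinicians who never saw the intervention.** The article does not support that. It promises descriptive comparison by arm, and its model-based arm comparisons cover only CritCom and the exploratory outcomes.

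**A reader might also infer that the pilot's primary conclusions rest on faulty p-values.** They do not. Descriptive levels are reported first, and which factors influence them is a further question.

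**The sizes depend on assumptions.** This is true. At ICC 0.01 the inflation is modest, and the large figures need a higher ICC.

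**The article promises suitable alternative tests if assumptions fail** (Missing data section). That clause is generic and does not mention clustering, so it does not cure the gap.

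**The 4-versus-8 conflict disappears if each hospital rates after its own delivery.** Table 2's data-collection window is set per hospital, which fits that reading. But the article never says so, and its last survey comes before the wait-list hospitals receive anything.

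**Conclusion.** The point holds in a limited form. The primary clinician ratings are assigned rank tests with no allowance for hospital clustering or repeat ratings, in a section that makes this allowance for CritCom. A clinician-level test of a hospital-level factor would have a true error rate of about 7–11% at ICC 0.01 and 16–29% at ICC 0.05 (simulated, 4 v 4 hospitals, 20 to 60 respondents each), against a nominal 5%. The ICC, respondent numbers and significance level are assumed. Hospital-level rank tests avoid the error but can tell little with 8 hospitals and almost nothing with 4.

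The conflict over who rates depends on none of these assumptions: Table 2 and the Implementation outcomes section cannot both describe the trial-period survey.

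Severity is moderate. The pilot is mainly descriptive, and the descriptive levels of the ratings do not depend on the tests.

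**What to change.** 1. **Name the raters.** State that during the randomised period only intervention-arm clinicians complete these ratings, and correct Table 2 to match. If wait-list hospitals are meant to rate after their own later delivery, say so, give the timing, and report them separately. That follow-up is optional; rating at 1 and 6 months would extend data collection by at least six months beyond the later delivery.
2. **Change the analysis of organizational factors.** Replace the unadjusted clinician-level rank tests with descriptive estimates by hospital and overall. Take intervals from hospital-level summaries, or from a model with hospital and clinician random terms as already planned for CritCom. With only 4 hospitals such a model estimates the between-hospital variance poorly, so the hospital-level summaries should be shown in any case.
3. **Label these analyses exploratory**, and name the comparison groups for any rank test that is kept. Analyse the 1- and 6-month ratings separately, or allow for the pairing.

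**Cost.** Apart from the optional follow-up, this is a change of analysis wording and one table entry. The price is wider intervals and fewer p-values. The raters should be settled before the surveys go out, because the respondent set cannot be repaired afterwards.

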#### Study settings and recruitment

Eight hospitals will be identified from the lowest quartile of communication quality based on prior CritCom data and measured as the overall CritCom score. Previous site leads will be contacted for study participation. In partnership with the local site lead, the research team will send emails to all clinicians who meet the inclusion criteria. Identified participants will include all clinicians who care for hospitalized children with cancer at risk of deterioration. We will use marketing and materials at the hospital to increase awareness and will send up to four emails to complete the survey instruments at each time point.

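### If the hospital random term is only an intercept, hospital-level drift drops out of the CritCom change contrast and the interval can be too narrow; the role of baseline and the degrees of freedom need stating

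*Protocol article*

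**What the plan says.** The trial is small in clusters. Study settings and recruitment says: "Eight hospitals will be identified from the lowest quartile of communication quality based on prior CritCom data". Randomization to intervention adds: "Hospitals will be randomized to either the multilevel intervention or a wait list control using a 1:1 ratio". I read this as 4 hospitals against 4.

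The Measures section of Aim 3 makes the change in CritCom score from baseline to 6 months the primary effectiveness outcome. Of its level it says: "The CritCom measure is collected at the individual level but will be analyzed as a hospital-level outcome". Scores are taken at enrolment, 1 month and 6 months.

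Data analysis specifies a linear mixed model with intervention as a fixed effect, "along with randomization assignment, baseline score, time, and the interaction between time and intervention". The effect is estimated "using a linear contrast to estimate the mean difference in communication quality (CritCom scores overall and by domain) from baseline to 6 months". Clustering is handled in one sentence: "To account for clustering due to individual- and hospital-level repeated measurements, we will include random terms for both in our mixed model". The section does not say whether the hospital term is an intercept, a slope or hospital-by-time. It does not say whether baseline is an outcome row, a covariate or both, and it names no degrees-of-freedom method. The same model is to be reused for the exploratory provider and patient outcomes.

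**The concern.** A random intercept is a constant for its hospital or clinician, so subtracting baseline from 6 months removes it. On the ordinary reading of the sentence (one intercept per person, one per hospital), only residual error is left in the contrast. Each clinician's change then counts as independent evidence.

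Hospitals were randomised, though, and hospital means can move together between surveys for reasons unrelated to the intervention. That shared movement is hospital-by-time variance. It does not average out over clinicians within a hospital, only over hospitals, and there are 4 per arm.

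The article itself expects hospitals to respond differently: Training provides for tailoring by hospital, and Data analysis plans hospital-specific analyses of heterogeneity. Assuming no hospital-by-time variance sits badly with both.

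At stake is the interval around the preliminary effect. The pilot is meant to prepare a hybrid implementation-effectiveness trial, and an interval that is too narrow makes a chance difference between two sets of four hospitals look better established than it is.

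**Working it through.** The article gives no standard error, interval, ICC or sample-size figure for this outcome, so there is nothing to reproduce. The size has to be explored under assumptions.

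**From the article:** 8 hospitals at 1:1, so 4 per arm; 3 measurement times; contrast from baseline to 6 months.

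**Assumed:** m clinicians per hospital; total variance 1; ICC ρ; cluster autocorrelation CAC; half of the within-hospital variance stable for each person. Then:

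- hospital-by-time variance: vHT = ρ(1 − CAC)
- residual variance: ve = 0.5(1 − ρ)

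**Reading A: baseline is an outcome row, intercepts only.** One hospital's mean change has variance 2vHT + 2ve/m. The difference between two means of 4 hospitals multiplies this by 1/4 + 1/4 = 0.5:

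- true SE = √(vHT + ve/m)

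The intercepts-only model puts vHT into the residual and divides everything by m:

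- model SE ≈ √((ve + vHT)/m)

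The squared ratio is 1 + (m − 1)·vHT/(vHT + ve). The number of hospitals does not appear in it.

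Example with m = 50, ρ = 0.05, CAC = 0.8: vHT = 0.05 × 0.2 = 0.01 and ve = 0.5 × 0.95 = 0.475.

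- true SE = √(0.01 + 0.0095) = √0.0195 = 0.140
- model SE = √(0.485/50) = √0.0097 = 0.098
- ratio = √(1 + 49 × 0.01/0.485) = √2.01 = 1.42

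Selected cells follow. Coverage comes from 2,000 simulated trials per cell, with 1.96 as the multiplier. Widths are of the 95% interval in SD units; the last column uses the 8 hospital mean changes with t on 6 df (2.45).

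| m | ICC | CAC | true SE | model SE | ratio | coverage | width, intercepts only | width, hospital means |
|---|---|---|---|---|---|---|---|---|
| 50 | 0.05 | 1 | 0.097 | 0.097 | 1.00 | 95% | 0.38 | 0.46 |
| 20 | 0.02 | 0.9 | 0.163 | 0.157 | 1.04 | 93% | 0.61 | 0.77 |
| 20 | 0.05 | 0.8 | 0.184 | 0.156 | 1.18 | 90% | 0.61 | 0.86 |
| 50 | 0.05 | 0.8 | 0.140 | 0.098 | 1.42 | 84% | 0.39 | 0.65 |
| 100 | 0.10 | 0.8 | 0.157 | 0.069 | 2.28 | 62% | 0.27 | 0.74 |
| 100 | 0.10 | 0.5 | 0.233 | 0.071 | 3.30 | 45% | 0.27 | 1.09 |

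Over m 20 to 100, ICC 0.02 to 0.10 and CAC 0.5 to 0.9, the ratio runs from 1.04 to 3.30 and coverage from 93% down to 45%. At CAC = 1 the ratio is 1.00.

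The result does not hang on the stable share of one half. With 0.6 stable, m = 40, ρ = 0.05 and CAC = 0.8, ve = 0.4 × 0.95 = 0.38. The true variance is 0.01 + 0.0095 = 0.0195, the model variance is 0.39/40 = 0.00975, and the ratio is √2 = 1.41.

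**Degrees of freedom.** With the hospital-mean SE but multiplier 1.96, coverage is still only about 90%. With t on 6 df it is 94 to 96% in every cell. This part is due to having 8 clusters.

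**Reading B: baseline is a covariate, the 1- and 6-month scores are outcomes.** The hospital intercept stays in the arm comparison and absorbs much of the drift. At CAC = 0.8:

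| m | ICC | empirical/model SE | coverage, 1.96 | coverage, t on 6 df |
|---|---|---|---|---|
| 20 | 0.05 | 0.94 | 93% | 99% |
| 20 | 0.10 | 1.06 | 89% | 97% |
| 50 | 0.05 | 0.93 | 92% | 95% |
| 50 | 0.10 | 1.26 | 87% | 91% |

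These cells have only 120 to 150 runs each, so coverage is known to about 2 to 3 percentage points (for example √(0.9 × 0.1/120) = 0.027). The shortfall is mainly a matter of degrees of freedom. The last cell may hold some remainder, which so few runs cannot settle.

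**The case against.** The strongest reply is that the text does not say what Reading A needs. It speaks of random terms at both levels and never calls them intercepts or limits the hospital to one. A hospital-by-time term would fit the wording, and covariance structure is often left to an analysis plan, which is not at hand. This stands: a reader might infer that the trial is committed to one intercept per hospital, and the article does not support that.

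Baseline score is also a listed covariate, which permits Reading B, where the damage is modest. This stands too, with a limit. If baseline is not a level of time, the time and interaction terms cannot form the contrast the article states. So the listed covariate and the stated contrast do not settle on one model.

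The conflict with Measures is softer than it looks. A mixed model with a hospital term can describe hospital communication quality, and Data analysis promises work at both levels. There is a tension only if the hospital carries no error in the change contrast.

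Finally, the article says the pilot is not powered to test effectiveness and states no decision rule for CritCom. It is therefore not supported to speak of an inflated false-positive rate as a consequence for a trial decision. An interval that will inform planning should still be calibrated.

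**Conclusion.** The concern holds conditionally. On Reading A the CritCom interval leaves out hospital-by-time variance and can be too narrow, with a true-to-model SE ratio of about 1.04 to 3.3 over the assumed ranges and no shortfall in the SE if hospitals do not drift. On Reading B coverage is about 87 to 93% with a normal quantile at autocorrelation 0.8, mainly because of too few degrees of freedom.

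Two stronger statements are tempting and not supported. One is that the interval is far too narrow: cluster size, ICC and autocorrelation are all assumptions here, and the low end of the range is a 4% understatement. The other is that 8 clusters cause the omission: the SE ratio does not depend on the number of hospitals, and the small number adds a separate degrees-of-freedom problem.

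The point estimate is not in question. Importance is moderate: the affected quantity is a preliminary effect in an unpowered pilot, but it is the primary effectiveness outcome and its model is reused for other outcomes.

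**What to change.** State first whether baseline CritCom is an outcome row or a covariate. Then choose one of two analyses. They are distinct and will not give the same interval.

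1. Keep the mixed model, add a hospital-by-time random term, and use Kenward-Roger or Satterthwaite degrees of freedom.
2. Analyse the 8 hospital means: either the change compared between arms on 6 df, or the 6-month mean regressed on arm and baseline mean on 5 df. This fits the statement in Measures that CritCom "will be analyzed as a hospital-level outcome". The baseline-adjusted form also suits a randomisation balanced on baseline CritCom.

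Report the estimated ICC and cluster autocorrelation as inputs to the future trial, noting that 8 hospitals will estimate them imprecisely.

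The cost is a sentence or two of text and a wider interval: in the middle example, 0.65 SD in place of 0.39 SD. No extra data are needed.
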